# Clinical effectiveness, cost-effectiveness and process evaluation of group schema therapy for eating disorders: study protocol for a multicenter randomized controlled trial

**DOI:** 10.1186/s40359-024-01624-w

**Published:** 2024-03-04

**Keywords:** (Atypical) Anorexia nervosa, (Atypical) Bulimia nervosa, Clinical effectiveness, Cognitive behavioral therapy, Cost-effectiveness, Cost-utility, Eating disorders, Economic evaluation, Group schema therapy, Randomized controlled trial

## Abstract

**Background:**

Eating disorders (EDs), such as (atypical) Anorexia (AN) and Bulimia Nervosa (BN), are difficult to treat, causing socioeconomic impediments. Although enhanced cognitive behavioral therapy (CBT-E) is widely considered clinically effective, it may not be the most beneficial treatment for (atypical) AN and BN patients who do not show a rapid response after the first 4 weeks (8 sessions) of a CBT-E treatment. Alternatively, group schema therapy (GST) may be a valuable treatment for this ED population. Even though GST for EDs has yielded promising preliminary findings, the current body of evidence requires expansion. On top of that, data on cost-effectiveness is lacking. In light of these gaps, we aim to describe a protocol to examine whether GST is more (1) clinically effective and (2) cost-effective than CBT-E for (atypical) AN and BN patients, who do not show a rapid response after the first 4 weeks of treatment. Additionally, we will conduct (3) process evaluations for both treatments.

**Methods:**

Using a multicenter RCT design, 232 Dutch (atypical) AN and BN patients with a CBT-E referral will be recruited from five treatment centers. Clinical effectiveness and cost-effectiveness will be measured before treatment, directly after treatment, at 6 and at 12 months follow-up. In order to rate process evaluation, patient experiences and the degree to which treatments are implemented according to protocol will be measured. In order to assess the quality of life and the achievement of personalized goals, interviews will be conducted at the end of treatment. Data will be analyzed, using a regression-based approach to mixed modelling, multivariate sensitivity analyses and coding trees for qualitative data. We hypothesize GST to be superior to CBT-E in terms of clinical effectiveness and cost-effectiveness for patients who do not show a rapid response to the first 4 weeks of a CBT-E treatment.

**Discussion:**

To our knowledge, this is the first study protocol describing a multicenter RCT to explore the three aforementioned objectives. Related risks in performing the study protocol have been outlined. The expected findings may serve as a guide for healthcare stakeholders to optimize ED care trajectories.

**Trial registration:**

clinicaltrials.gov (NCT05812950).

**Supplementary Information:**

The online version contains supplementary material available at 10.1186/s40359-024-01624-w.

## Background

Eating disorders (EDs) are associated with decreased social, psychological, and physical functioning in individuals [1] and elevated premature mortality rates [2]. On a healthcare system level, EDs contribute substantially to the mental health burden. Between 2000 and 2018, the weighted mean of point ED prevalence across continents had increased from 3.5 to 7.8% [3].

In a similar vein, the collective ED disease burden is reflected through major socioeconomic constraints. On average, ED patients generate more healthcare expenses and have lower employment rates than people without ED [4]. According to Van Hoeken and Hoek [5], over 3.3 million healthy life years are lost worldwide annually due to EDs. In addition to that, these authors showed that ED patients generated a 48% increase in healthcare costs, compared to the general population, while EDs with comorbid other psychiatric disorders were associated with a 48% decrease in yearly earnings in those employed.

In clinical practice, enhanced cognitive behavioral therapy (CBT-E) is used as treatment for all types of EDs, because of its transdiagnostic applicability and effectiveness [6]. Even though CBT-E is clinically effective for a certain group of ED patients, it is presumably not the most clinically optimized treatment for patients with (atypical) Anorexia Nervosa (AN) or Bulimia Nervosa (BN). More specifically, CBT-E is characterized by a substantial dropout rate: 20–54% in randomized controlled trials [6], especially in AN [7–9]. In general, only 30–50% of ED patients achieve clinical remission after CBT-E treatment [6, 10].

Although certain ED patients are greatly capable of challenging their own belief systems during treatment, they are generally unable to modify deeply held core beliefs [11]. In line with this observation, many ED cases reflect a complex intertwining between eating pathology and comorbid personality pathology [11–13], including clinical perfectionism [14]. Moreover, comorbid personality pathology increases the risk of attrition and is associated with greater psychopathology after treatment [11]. Albeit uncertain, not all (atypical) AN and BN patients may benefit sufficiently from CBT-E, perhaps due to a lack of emphasis on deeply rooted core beliefs.

In light of the findings above, schema therapy (ST) may be a clinically effective alternative that offers potential for addressing comorbid personality pathology. In short, ST provides an integrative approach that is fundamentally geared towards treating people with deeply entrenched self-identity difficulties and interpersonal problems, which are reflected through maladaptive schemas and schema modes [15]. Using these theoretical foundations, ST is either delivered individually or in a group setting (GST) in clinical practice. While individual ST [16, 17] and GST [18] were already found to be clinically effective and cost-effective for treating personality disorders, the rationale underlying their application for effectively treating EDs has also been documented [19]. The hypothesis is that EDs are characterized by overdeveloped coping modes that either avoid schema activation or manage affect when schemas are triggered. In general, the theoretical foundations regarding schemas and schema modes have already been applied to eating disorders in certain pilot studies, which were considered promising [20–22]. Contrary to individual ST, GST aims to establish a collective sense of awareness among ED patients regarding their shared emotional needs and applied schemas and coping mechanisms, building upon therapeutic alliance in the context of a supportive group environment. As a result, the GST approach may prevent drop-out rates among ED patients [23], which is a major hurdle in current CBT-E delivery formats.

New studies with adequate control groups are needed in order to expand the preliminary body of evidence on GST for eating disorders. This is important, since current CBT-E does not automatically address personality pathology in patients with persisting EDs, leaving many of them without adequate potential for recovery [8, 24]. In general, (atypical) AN and BN patients not showing an early treatment response after the first 4 weeks of a CBT-E treatment may be at an elevated risk of dropping out and achieving suboptimal clinical outcomes after a full CBT-E trajectory [25–27]. Therefore, the current study protocol will focus on ED patients who do not show a significant reduction in ED symptoms after the first 4 weeks (8 sessions) of CBT-E, which is the first of four CBT-E treatment phases [28].

Furthermore, to our current opinion studies on the cost-effectiveness of GST for ED patients are lacking. In accordance with a cost-effectiveness paradigm to facilitate value-based healthcare [29–31], cost evaluations of GST and CBT-E in proportion to their clinical outcomes are indispensable for the purpose of optimizing care trajectories for (atypical) AN and BN patients. Therefore, the current study protocol will examine the clinical effectiveness and cost-effectiveness of GST. This protocol aligns neatly with the Research Agenda in Dutch Mental Healthcare, which aims to improve two aspects: clinical value and affordability of mental healthcare in The Netherlands [32].

Implementation feasibility of new treatments in clinical practice is important. Ideally, new treatments should be easily implementable in clinical practice in order to avoid long term implementation barriers and to increase treatment successes [33]. Similarly, therapeutic alliance and patient experiences during treatment are generally considered predictors of clinical outcomes among ED patients [34]. In order to account for these predictive effects, process evaluations need to be conducted among participating ED patients and therapists during the implementation process of GST and CBT-E.

The current paper presents a comprehensive study protocol to examine the clinical effectiveness, cost-effectiveness and process evaluation of GST, compared to CBT-E, for patients with (atypical) AN or BN who do not show a significant reduction in ED symptoms after the first 4 weeks (8 sessions) of CBT-E treatment.

### Objectives

The current study protocol will test hypotheses and answer research questions from three distinct research areas:

#### Clinical effectiveness

We hypothesize GST to be more effective in terms of promoting treatment adherence and reducing ED severity, early maladaptive schema’s, dysfunctional schema modes and increasing quality of life, compared to CBT-E for (atypical) AN and BN patients not showing a rapid response after the first 8 CBT-E sessions.

#### Economic evaluation

We hypothesize GST to be more cost-effective from a societal perspective, compared to CBT-E, in terms of costs, effects and utilities.

#### Process evaluation

Within the process evaluation, research questions are (1) To what degree have the GST treatment and CBT-E treatment been delivered according to protocol? (2) What are reported reasons for protocol deviation in GST and CBT-E? and (3) What are the experiences of patients regarding GST and CBT-E?

### Methods/Design

#### Design

A multicenter randomized controlled superiority trial will be applied, in which GST is defined as the intervention treatment and continued CBT-E as the control treatment. Initially, patients assigned to a CBT-E treatment are eligible for screening. Before and after the first 8 CBT-E sessions, patients will be screened, using the Eating Disorder Examination Questionnaire (EDE-Q). Patients failing to reach a statistically defined cut-off score for reliable improvement on the EDE-Q (determined with the Reliable Change Index as described by Jacobson & Truax^35^), will be randomized to either GST or continued CBT-E as usual. These particular patients are called early non-responders to CBT-E. Conversely, patients reaching this cut-off score for reliable improvement on the EDE-Q will be excluded from further study participation prior to randomization and will continue their CBT-E treatment.

#### Randomization

Random allocation to the control group (continued CBT-E) or the intervention group (GST) will be conducted separately for each treatment location in a ratio of 1:2 by an automatized randomization software program after the completion of the post measurement. This ratio is due to the cluster effect in group-based therapy, which statistically requires more participants for the GST arm than for the continued CBT-E arm. Subsequent to randomization, participants in the GST arm and continued CBT-E arm will complete a baseline measurement (T0). After that, both treatments will start. Post-measurements (T1) will take place on the known end date of the treatment to which a participant is randomized. Follow-up measurements will take place 6 months (T2) and 12 months (T3) later, following initial completion of the entire treatment trajectory at T1. Several clinical measurement instruments are used, see Fig. 1. The current study protocol has been approved by the Medical Research Ethics Committee (MREC) Academic Hospital Maastricht/University Maastricht in The Netherlands, which was formally registered as: NL80491.068.22. The study is registered at ClinicalTrials.gov (registration number NCT05812950), and complies with the World Health Organization Trial Registration Data Set. Modifications to the protocol will be submitted as an amendment and will be examined by the MREC and will be adjusted in the trial registry.

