### Treatments

#### Intervention: Group Schema therapy (GST)

GST will consist of 26 weekly 90-minute group sessions, tailored to people with an ED. If necessary, GST can be supplemented with 8 individual sessions used for facilitating the GST process. The individual sessions can for example be used for imagery rescripting of adverse childhood experiences. Subsequent to randomization, patients may have to wait for at most three months before initiating their GST treatment in mental healthcare, as it is a half-open group, with an entry and exit moment every 13 weeks. During this waiting period, 5 individual treatment sessions will take place that focus on explaining the ST model, placing the ED symptoms and behaviors in the context of coping modes, and organizing these in a mode map conceptualization. This is an important foundation for the upcoming GST. The following sessions focus on recognizing and changing personal coping modes regarding eating disorder symptoms and underlying early maladaptive schemas. These sessions are also aimed at developing and strengthening the healthy adult mode. In doing so, GST combines interpersonal, experiential, cognitive and behavioral elements in a unified ST approach. On top of that, a psycho-education webinar will be organized for relatives.

**Theoretical framework for GST: a group format of ST.** In short, ST provides an integrative approach that is fundamentally geared towards treating people with deeply entrenched self-identity difficulties and interpersonal problems, which are reflected through maladaptive schemas and schema modes [15]. In clinical practice, ST was deemed effective for treating personality disorders [16], including ST in a group setting [18]. On the one hand, maladaptive schemas refer to a pervasive pattern of beliefs regarding oneself and one’s relationship with others consisting of one’s memories, emotions, cognitions and bodily sensations. On the other hand, schema modes are characterized by one’s moment-to-moment thoughts, feelings and behaviors when maladaptive schemas interact with coping mechanisms [23].

In terms of treatment delivery, ST emphasizes experiences, while CBT-E mainly emphasizes cognitions and behavior. In GST, the connection between participants in the group format is considered an amplifier for the effects of ST. On top of that, GST ensures a healthy therapeutic relationship to provide corrective experiences in favor of the patient’s needs during treatment [23].

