Subsequent to randomization, participants will complete measures before continued CBT-E or the start of GST (T0), immediately after the confirmed end date of treatment (T1), and 6 months (T2) and 12 months (T3) following completion of treatment. In addition to measuring perceived ED schemas, data on quality of life and healthcare service use will also be gathered on these occasions. Data on process evaluations, as assessed by session rating scales and patient registration files, will be collected during each treatment session of phase 1 CBT-E, continued CBT-E, and GST. After treatment (T1), a representative sample of ED patients from both arms will be recruited to participate in a qualitative interview to gain deeper insights into their treatment experiences. Due to the nature of the interventions, blinding of therapists, interviewers, and patients is not possible. Below, all measures are stratified for clinical effectiveness, economic evaluation and process evaluation.

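### Five non-primary instruments have their only baseline after unblinded randomisation, and the article does not settle whether that baseline in the GST arm precedes or follows five individual schema-therapy sessions

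*Protocol article*

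**What the plan says.** The Randomization section of the protocol article allocates patients "by an automatized randomization software program after the completion of the post measurement", that is, after the EDE-Q that follows the first eight CBT-E sessions. The next step is T0: "Subsequent to randomization, participants in the GST arm and continued CBT-E arm will complete a baseline measurement (T0". The section then adds: "After that, both treatments will start".

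The Data collection section also places T0 after randomisation, but ties it to a different event: "participants will complete measures before continued CBT-E or the start of GST (T0". It further states that "blinding of therapists, interviewers, and patients is not possible".

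The section on the GST intervention says that after randomisation "patients may have to wait for at most three months before initiating their GST treatment in mental healthcare", because the group opens for entry every 13 weeks. It continues: "During this waiting period, 5 individual treatment sessions will take place that focus on explaining the ST model".

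In Table 1, the first measurement of the TIC-P, EQ-5D-5L, EDQOL, SMI-ED and BSI is at T0. The Clinical effectiveness part of the Data analysis section takes change from T0 to T1 and onwards, and compares the arms on it in mixed models.

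**The concern.** A baseline should be a value that allocation cannot have touched. Here five patient-completed instruments are first filled in after allocation, in a trial where patients cannot be blinded. The setting makes a reaction plausible: every randomised patient has just missed the cut-off for reliable improvement on CBT-E, and some then learn that they will continue with it while others move to something new. Hope or disappointment could change how a patient rates symptoms, modes or quality of life on that day. Any such difference between the arms at T0 carries into change from T0.

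Two things follow. First, patients who withdraw, or do not complete T0, after learning their arm have no baseline on these instruments, and this loss can differ between the arms. Second, if T0 in the GST arm is taken just before group entry, it could follow five individual sessions built on the schema model. The GST baseline would then already contain treatment, and part of that arm's costs and QALYs after randomisation could lie outside T0 to T3.

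At stake are the secondary outcomes measured with these instruments and the economic evaluation, which takes utilities from the EQ-5D-5L and societal costs from the TIC-P.

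**Working it through.** **Step 1: which baselines are exposed.** From Table 1, the last value before randomisation is:

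| Instrument | Last value before randomisation | Value at T0 |
|---|---|---|
| EDE-Q (primary) | post-measure of phase 1 | no |
| YSQ-S3 | pre-measure | no |
| BMI | pre-measure | yes |
| TIC-P, EQ-5D-5L, EDQOL, SMI-ED, BSI | none | yes |

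Five instruments depend on T0 alone. The CPQ and CTQ-SF are taken only at the pre-measure and have no follow-up. The planned total of 232 was set for the primary outcome and does not bear on this point.

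**Step 2: when T0 occurs in the GST arm.** Three statements have to be read together.

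- Randomization: the order is allocation, T0, then the start of both treatments.
- Data collection: T0 comes before the start of GST.
- GST intervention: the wait, with its five sessions, comes before GST is initiated.

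A T0 taken directly after allocation satisfies all three. A T0 taken at the end of the wait also satisfies all three, provided that GST starts with the first group session, which is how the third statement uses the term. If the five sessions count as part of the treatment, only the early T0 fits. The text does not say which is meant.

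**Step 3: how a shift at T0 carries through.** The documents give no size, so the values here are assumed. Let s be the between-arm difference at T0 caused by knowledge of the arm or by early sessions, in SD units, positive when GST looks better. Let b be the slope with which T0 is adjusted for; b = 1 is a plain change score. Then

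estimated difference = true difference − b × s.

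| s | b × s at b = 0.5 | at b = 0.7 | at b = 1.0 |
|---|---|---|---|
| 0.1 | 0.05 | 0.07 | 0.10 |
| 0.2 | 0.10 | 0.14 | 0.20 |
| 0.3 | 0.15 | 0.21 | 0.30 |

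Take a true difference of 0.50, borrowed from the sample size section for illustration only. The estimate would lie between 0.50 − 0.05 = 0.45 and 0.50 − 0.30 = 0.20. With s of the opposite sign it would lie between 0.55 and 0.80.

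**Step 4: the economic window.** T1 is at the end of each patient's own treatment, and T3 is 12 months (52 weeks) later. GST has 26 weekly group sessions, so group entry to T3 is 26 + 52 = 78 weeks. With the longest wait, randomisation to T3 is 13 + 78 = 91 weeks. Continued CBT-E has 12 to 32 sessions. At one session a week (assumed; the article gives no frequency for this part), T3 falls at 12 + 52 = 64 to 32 + 52 = 84 weeks. The windows differ in length between and within the arms even when they all start at randomisation.

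**The case against.** The strongest reply is that the trial's main result is untouched. The EDE-Q is measured twice before randomisation, and the YSQ-S3, the secondary outcome listed first, has its baseline before phase 1. A reader might infer that every secondary clinical contrast is biased; Table 1 does not support that. This part of the reply stands in full.

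A reader might also infer that the GST baseline certainly contains five sessions of treatment. The Randomization section, read alone, puts T0 before any treatment, and Fig. 1, not available here, may settle the timing. The documents support a need to reconcile the text, not a claim of contamination.

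It is tempting to value the wait at 13/52 of a year times a utility and call that the error in the QALY comparison. That product is everything a patient accrues over the longest possible wait. On a common horizon the error depends on the utility difference between the arms in the uncounted weeks, which the documents do not give. Nor is the cost of the five sessions shown to be lost: intervention costs are a separate bottom-up category, and therapists complete registration files after each session.

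The allocation effect itself is assumed and could go either way. No sentence says that patients learn their arm before T0. Equally, none describes withholding it, and T0 follows randomisation in a trial declared unblinded. Intention-to-treat and missing-data methods are planned, but they cannot supply a pre-randomisation score that was never collected.

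**Conclusion.** The point holds in two parts of different certainty.

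Certain from the text: the TIC-P, EQ-5D-5L, EDQOL, SMI-ED and BSI have no value before randomisation, patients are not blinded, and change is measured from T0. These baselines are open to an allocation effect of unknown size and direction, and patients lost between randomisation and T0 have none. This rests on one inference, that the arm is known by the time T0 is completed.

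Unsettled by the text: whether T0 in the GST arm precedes or follows the wait and its five individual sessions. If it follows, the GST baseline already contains treatment, and part of that arm's costs and QALYs after randomisation could fall outside T0 to T3. The first part stands whichever reading is right.

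The primary EDE-Q and the YSQ-S3 are not affected, and BMI has an earlier value. No figure for the bias can be drawn from the documents; the range of 0.05 to 0.30 SD only shows how assumed shifts would carry through. The matter deserves correction because it touches several secondary outcomes and the economic evaluation, and because later analysis cannot repair it.

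**What to change.** - Once the EDE-Q after phase 1 shows no reliable change, have the online system open the T0 battery, and trigger randomisation on its completion. Consent is already given before phase 1, so no new consent step is needed.
- Reconcile the Randomization, GST intervention and Data collection sections so that they state one timing for T0, before allocation, and say how the five individual sessions relate to the start of GST.
- Count costs and QALYs from randomisation over the same calendar length in both arms. A common start alone does not equalise the horizons, because T1 to T3 follow each patient's own end of treatment.
- Adjust QALYs for the pre-randomisation EQ-5D-5L utility.

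The change reorders two steps in a data system that the article describes as adaptable, and amends a few sentences. It adds no questionnaires. The downsides are that randomisation waits for a battery already planned (a full measurement may take up to two hours), that patients who do not complete it are not randomised, and that the GST baseline may precede group entry by up to three months. Loss at this step then occurs before allocation and cannot differ by arm.

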#### Control treatment: individual enhanced cognitive behavioral therapy for eating disorders (CBT-E)

In general, CBT-E is a transdiagnostic ED treatment, meaning that it is widely used for most diagnosed EDs in mental healthcare. In addition to that, it is also considered the current standard of care for most EDs. An entire CBT-E trajectory consists of 20–40 individual sessions, each of which will last 60 min at most. In the current protocol, the first 8 CBT-E sessions for a patient will take place before randomization (phase 1 CBT-E). After being randomized to the continued CBT-E arm, the remaining 12–32 individual sessions will take place.

From a theoretical perspective, CBT-E is based on a so-called transdiagnostic CBT model consisting of four phases. In phase one, patients formulate a personal goal, in which they learn to monitor and establish regular eating behaviors in order to address their eating disorder. In doing so, patients are offered psycho-education on factors that are maintaining their eating disorder. In phase two, consisting of one session, a more specific treatment plan is developed, based on an evaluation of the first phase. During phase three, the identified main mechanisms that are hypothesized to maintain the patient’s ED are addressed. These are (1) an excessive evaluation of body image, (2) dietary restraint, and (3) events, mood and eating. Subsequently, a relapse plan is developed in order to maintain the newly established eating behaviors when faced with these challenging mechanisms. Lastly, phase four aims to evaluate and sustain the total progress that has been achieved during the prior phases.

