#### Economic evaluation

**Base-case analysis.** Using a micro-costing and bottom-up approach, total costs will be approximated from a societal perspective in the GST arm and the continued CBT-E arm, in line with recent best practices [52]. Essentially, each element of service use will be multiplied by an appropriate unit cost in euros. If necessary, unit costs will be updated, using the 2023 consumer price index [55]. Relevant unit costs for each type of service are outlined in contemporary Dutch costing manuals for healthcare services [56, 57]. Intervention costs, healthcare costs, patient and family costs and productivity losses for unpaid work, paid work and education will be estimated. Productivity losses will be quantified, using a friction cost approach that is confined to the time period required to replace one sick employee. In case of major uncertainty surrounding the abovementioned analyses, cost estimates will be founded on the most conservative assumptions.

Primarily, economic evaluations aim to compare the additional costs and outcomes of GST to those of CBT-E. In the economic evaluation of the current protocol, collected data will be used to conduct a cost-effectiveness analysis (CEA) and a cost-utility analysis (CUA). On the one hand, a CEA expresses all clinical treatment effects of GST and CBT-E relative to their economic costs, using the incremental cost-effectiveness ratio (ICER). On the other hand, a CUA aims to compare all gains in quality adjusted life years (QALYs) of GST and CBT-E to their respective economic costs, using the incremental cost-utility ratio (ICUR).

In short, the ICER is aimed at dividing the difference in treatment effects of GST and CBT-E by the difference in total costs of both treatments. For instance, the total difference in clinical EDE-Q gains of both GST and CBT-E can be weighed against the cost differences of both treatments. Using a similar incremental cost-utility ratio (ICUR), the difference in QALY gains of both treatments is divided by their respective cost differences. QALYs are computed based on the measured EQ-5D-5 L data, using converted EuroQol utility scores [58].

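### Costs and QALYs are collected on a clock tied to the end of treatment, so at likely CBT-E session rates they cover a longer period, on average, in GST than in continued CBT-E

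*Protocol article*

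**What the plan says.** The Randomization section sets the clock: "Post-measurements (T1) will take place on the known end date of the treatment to which a participant is randomized". It continues: "Follow-up measurements will take place 6 months (T2) and 12 months (T3) later, following initial completion of the entire treatment trajectory at T1". The Data collection section and the footnote to Table 1 repeat this anchoring.

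Treatment length differs by arm. For the intervention, "GST will consist of 26 weekly 90-minute group sessions, tailored to people with an ED", and before that "patients may have to wait for at most three months before initiating their GST treatment"; five individual sessions fill the wait. For the control, "After being randomized to the continued CBT-E arm, the remaining 12–32 individual sessions will take place". No session rate is given for this part of CBT-E. The only rate in the article is for phase 1, eight sessions in four weeks.

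Table 1 places TIC-P and EQ-5D-5L at T0, T1, T2 and T3. In the Economic evaluation part of the analysis section, "total costs will be approximated from a societal perspective in the GST arm and the continued CBT-E arm", QALYs come from the EQ-5D-5L data, and the arm differences form the ICER and ICUR. No common horizon, truncation or rescaling to equal time is described. The only stated horizon, three years, belongs to the budget impact analysis. For clinical outcomes, the arms are compared at each labelled time point.

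**The concern.** A QALY is utility multiplied by time, and a cost total grows with the weeks over which it is collected. If one arm is observed longer because its treatment takes longer, subtracting the totals gives a difference even when the treatments are equivalent. Bootstrapping describes sampling uncertainty around that difference; it does not remove the systematic part. Cost-effectiveness is one of the trial's three stated objectives, so the incremental cost and QALY figures matter.

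The primary outcome is touched in a milder way. EDE-Q at T1, T2 and T3 is compared between patients who are at different distances from randomisation, so the contrast mixes treatment with elapsed time.

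**Working it through.** The article gives no time from randomisation to T1 or T3 and no horizon for the economic evaluation, so there is no figure on this point to reproduce. The sample size does reproduce (86 per arm; 1 + 7 × 0.10 = 1.70; 1.70 × 86 = 146; 146 + 86 = 232) and does not depend on this issue.

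**Inputs.** GST: 26 weeks, plus a wait of 0–13 weeks (three months taken as 13 weeks). The optional individual GST sessions are assumed to fall within the 26 weeks. CBT-E: 12–32 sessions, midpoint 22. T3 = T1 + 52 weeks. The CBT-E rate after session 8 is an assumption and is varied. Midpoints stand in for means, which the article does not give.

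**GST, from randomisation.** T1 = 26 to 26 + 13 = 39 weeks. T3 = 78 to 91 weeks, midpoint 84.5. If T0 is taken after the wait, T0 to T3 is 26 + 52 = 78 weeks.

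**CBT-E, from randomisation.** T1 = sessions ÷ rate.

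| CBT-E sessions per week (assumed) | T1, weeks | T3, weeks | T3 midpoint | GST minus CBT-E, from randomisation | GST minus CBT-E, T0 after wait |
|---|---|---|---|---|---|
| 2 | 6–16 | 58–68 | 63 | 84.5 − 63 = 21.5 | 78 − 63 = 15 |
| 1 | 12–32 | 64–84 | 74 | 84.5 − 74 = 10.5 | 78 − 74 = 4 |
| 0.75 | 16–42.7 | 68–94.7 | 81.3 | 3.2 | −3.3 |
| 0.5 | 24–64 | 76–116 | 96 | −11.5 | −18 |

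**Break-even rate.** The midpoint gap is zero when 22 ÷ rate = 32.5, so rate = 0.68 per week; with T0 after the wait, 22 ÷ 26 = 0.85 per week.

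**Individual pairs.** At one session per week the gap runs from 26 − 32 = −6 to 39 − 12 = +27 weeks. At two per week it runs from 26 − 16 = +10 to 39 − 6 = +33.

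**QALYs with no treatment effect.** Artefact = gap ÷ 52 × utility, with utility assumed equal and constant at 0.7 (0.6–0.8):
- 4 weeks: 0.05 (0.05–0.06)
- 10.5 weeks: 0.14 (0.12–0.16)
- 15 weeks: 0.20 (0.17–0.23)
- 21.5 weeks: 0.29 (0.25–0.33)

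**Position of T0.** The Randomization section puts T0 after randomisation and before both treatments; the Data collection section puts it before continued CBT-E or the start of GST. Neither says whether it comes before or after the GST wait. If after, the gap shrinks, but the costs of the wait and its five sessions drop out of the T0–T3 window.

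**EDE-Q.** Table 1 has no EDE-Q at T0. The last value before treatment is the post-measure, taken before randomisation, so the interval to T1 includes the GST wait wherever T0 sits.

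**The case against.** The strongest reply is that the article states no accumulation window. Horizon and interpolation rules are commonly left to a full protocol or analysis plan, and a plan that annualises or truncates would remove the problem. That stands in part: a reader might infer that the article commits to summing over unequal windows, and it does not say so. But it does fix when the data are collected, and it takes arm totals and differences from those data with no common period. Followed as written, that schedule can bias the result.

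The gap also rests on an unstated session rate. This stands: it is an arm average over a range, and at weekly sessions a 32-session CBT-E patient outlasts a GST patient who did not wait. It would be wrong to say that every GST patient is followed longer.

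For EDE-Q, comparing the arms at the end of treatment and 6 and 12 months later is a coherent clinical question. That stands too.

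Three stronger readings are tempting and lack support:
- That later EDE-Q measurement favours GST. This needs scores to improve steadily with time; the article gives no drift rate, and these are early non-responders.
- That the artefact exceeds any real QALY difference. The article gives no expected difference to compare it with.
- That CBT-E patients who stop early are measured earliest. The known end date of the allocated treatment can be read as the scheduled end, not the date of dropout.

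**Conclusion.** The point holds as an average statement about the economic data. The T0–T3 period is longer in GST unless CBT-E runs slower than about 0.68 sessions per week, or 0.85 if T0 follows the wait. The midpoint excess is 10.5 to 21.5 weeks counted from randomisation, or 4 to 15 weeks counted from a T0 after the wait, for CBT-E at one to two sessions per week. At a utility of 0.7 this is about 0.05–0.29 QALY in favour of GST that no treatment effect produced. Extra costs accrue over the same weeks and pull the other way on cost-effectiveness; the article gives no weekly cost, so no net euro figure can be stated. For EDE-Q the comparison is at unequal times since randomisation, and neither the size nor the direction of any bias can be derived from the article.

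**What to change.** - **Economic base case.** Accumulate costs and QALYs from randomisation to one horizon common to both arms and inside every scheduled follow-up. Fifty-two weeks meets this at any CBT-E rate, because T3 is always 52 weeks after T1. A horizon of 64 weeks would not: it assumes weekly sessions, and at two per week the earliest T3 is week 58. Interpolate EQ-5D-5L and TIC-P between actual measurement dates, and count the GST wait and its five sessions.
- **T0.** State that it is taken at the same point after randomisation in both arms.
- **EDE-Q.** Keep the end-of-treatment comparison. Record actual weeks since randomisation and report, beside it, the mixed-model arm difference at a common week.

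The cost is mainly wording and the use of recorded dates; if the T0 statement changes current practice, it goes through the amendment route that the article describes. The downside is that T3 lies beyond a 52-week horizon. In GST, T2 already falls at weeks 52–65 (T1 plus 26 weeks), so GST T3 data would serve a longer-horizon sensitivity analysis. In CBT-E, T3 is needed for interpolation whenever T2 falls before week 52. Neither treatment changes, and N = 232 stays.
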